### Secondary endpoints

As a secondary endpoint, there is the issue of biomarkers for risk evaluation, treatment outcomes and treatment evaluation.

Statistical analysis for this measure has been done in collaboration with associate professor [name], Institute of Psychiatry, King's College, London, England, when he

Study protocol: PRIOTAB---RCT, EudraCT 2014 ---000647 ---32

Version number 2014:2. Final version. Version date 140519.

special expertise on the method of analysis to be used -- Unsupervised Machine Learning. It is a method that is adapted to integrate large amounts of clinical data including MRI-based to clinically meaningful dimensions in search of biomarkers, including MRI-based to clinically meaningful dimensions. He has published several articles on the method, see, for example, the 2012 review (29).

#### Study size

The size of the study is motivated by the secondary objectives and not the primary. Ass [name] recommendation on study size for the secondary objectives is, based on study design in general, N=30 in each treatment arm in PRIOTAB-RCT, (N=60), as well as equal number of controls for comparison in PRIOTAB-- CC.

Konfidentiellt

## Statistical Analysis Plan

The statistical analysis will proceed as stated in the study protocol.

The primary endpoint is the composite risk score, which is measured on a range between zero and 15 points. The null hypothesis is that the mean change in the composite risk score between baseline and the two-week follow up in the active group is equal to that in the placebo group. We will test this hypothesis with a two-sided t-test at the 0.0294-level. The level is lower than 0.05 to take into account the testing at the interim analysis, as stated in the protocol.

In addition to the primary analysis, we will perform secondary analyses to evaluate differences between the treatment groups with respect to each of the following outcomes separately:

1. Composite risk score (numeric, ranging from 0 to 15)
2. Each of the five sub-scores (numeric ranging from 0 to 3)
3. The composite risk score in a subgroup stated as high risk (10 points or more)
4. European Quality of Life 5-Dimension 3-Level (EQ-5D-3L) index scores (numeric, ranging from 0 to 1)
5. EQ-5D-3L visual analogue scale (numeric, ranging from 0 to 100).

For the secondary analyses, we will include the observations collected at all time-points, baseline, two weeks, and ten weeks. We will analyze the longitudinal data with random effect regression models to allow for potential intra-individual correlation. The regression models will be linear for the numeric outcomes and logit-linked for the binary ones.

All the regression models will include the intercept, an indicator variable for the treatment group, and an indicator variable for the two-week time-point, an indicator variable for the ten-week time-point, and the two interaction (product) terms between the treatment indicator and the time-point indicators. Because patients were randomized to either treatment group, we will include no other covariates. The models will also include a patient-specific random intercept, which we will assume to follow a normal distribution independent of all the covariates.

We will test the difference between the two treatment groups with the Wald's test using the parameter estimates from the random effects regression models.

The number of possible side effects (binary variables) will be summarized by frequency tables by treatment group.

As of Morning 09:14, 25th of June 2019

[figure not shown]

[name]

[name]

[name]

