### Statistical analysis

#### Primary endpoint

This piece of text, about primary endpoint, is authored by our partner in the project in terms of statistics, [name], Core Facility for Biostatistics, Karolinska Institutet:

Primary endpoint is the composite risk score described above, which is measured on a range between 0 and 15 points.

Hypothesis for the primary endpoint of PRIOTAB---RCT: The mean change in the composite risk score between baseline and follow up in the degarelix group is equal to that in the placebo group.

The null hypothesis will be tested with a two---sided t---test. The mean change in the composite factor between baseline and follow---up will be compared between the degarelix and the placebo group.

The power to detect a difference between the degarelix and the placebo groups is calculated as follows. Based on clinical experience we make the following assumptions.

$\alpha=0.05$  (5% risk of rejecting a correct null hypothesis)

$\beta=0.20$  (20% risk of finding support for a false null hypothesis)

$\mu_1 - \mu_2$  (smallest clinically relevant difference in score change) =5

$\sigma = 3$

$a = 1,96$

$b = 0,842$

Statistical power=0.80 (1--  $\beta$ , i.e. 80% chance of rejecting a false null hypothesis) Effect size= $\mu_1 - \mu_2 / \sigma = 1.7$

Statistical power is calculated using this formula:

$$N = 2 * (a + b)^2 * \sigma^2 / (\mu_1 - \mu_2)^2 = 2 * (1,96 + 0,842)^2 * 3^2 / 5^2 = 6$$

Analysis population: The primary endpoint should be analyzed on the population that has taken the study drug and fully responded to the questionnaires so that a full risk assessment could be done on the basis of the composite measure.

To know if the patients should continue, a preliminary analysis of efficacy and safety should be performed when 20 individuals have passed the study. If the results indicate that degarelix has a clinically significant efficacy, there is ethical support to complete the study, so that we also achieve data enough to also be able answering questions related to the secondary endpoints (safety issues and biomarkers for risk assessment, biomarkers for prognosis of medication effect, and biomarkers of medication effect), otherwise PRIOTAB---RCT will be stopped. If the study continues, then a definite analysis will be performed when all of the individuals are collected.

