The p---values used at the interim analysis and at the possible final analysis will be 0.0294 [Pocock SJ, Group sequential methods in the design and analysis of clinical trials. *Biometrika*, 1977, 64 (2): 191–199]. These smaller p---values will preserve the overall level of the test at 0.05.

The blinding will be preserved by not disclosing the treatment group assignment to any of the parties involved, which comprise the patients, the doctors, and the analysts.

Patients that drop out will be included in an intention to treat analysis. Patients with missing values for the risk score at any time point will be excluded from the analysis. The analyses will be performed under the assumption that the missing data generating process is at random [Rubin DB. *Inference and missing data*. *Biometrika*, 1976, 63 (3): 581–592]. To assess the plausibility of this assumption, information on the reasons missingness will be elicited from the patients, doctors, or any other source available.

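### The primary t-test on change fixes the baseline slope at 1; estimating the slope would give a more precise treatment effect at almost no cost

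*Supplement*

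**What the plan says.** Protocol sections 6 (Primary endpoint) and 12 (Statistical analysis) define the primary comparison as a two-sided t-test on change: "The mean change in the composite factor between baseline and follow---up will be compared between the degarelix and the placebo group". The SAP fixes the time point at two weeks. It words the hypothesis of no difference as follows: "the mean change in the composite risk score between baseline and the two-week follow up in the active group is equal to that in the" (the comparator being placebo). It then names the test and its level: "We will test this hypothesis with a two-sided t-test at the 0.0294-level".

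The sample-size paragraph in section 12 assumes "Statistical power=0.80", two-sided alpha 0.05, sigma 3 and "smallest clinically relevant difference in score change) =5". The trial is larger than that calculation requires. Under Study size the protocol plans "N=30 in each treatment arm in PRIOTAB-RCT" and explains: "The size of the study is motivated by the secondary objectives and not the primary". The same section provides for an interim look at efficacy after 20 patients, and on missing data it says: "Patients with missing values for the risk score at any time point will be excluded from the analysis".

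Neither document specifies a baseline-adjusted analysis, primary or sensitivity. The SAP's secondary random-intercept models do not supply one. They treat baseline as one of three outcome times, keep a treatment main effect and admit no further covariates. With complete data, their two-week interaction term is the same difference in mean changes.

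**The concern.** A change score assumes that each extra baseline point carries over as a full extra point at follow-up. Where scores regress to the mean, the true slope is below 1 and subtraction over-corrects. The design gives reasons to expect this. The composite mixes self-ratings with performance tests, it is bounded at 0 and 15, and section 8 sets no minimum score for entry. The allocation described in sections 7 and 9 is not stratified by baseline risk, so nothing in the design prevents a chance difference between arms.

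Two things are at stake: a wider confidence interval than the data require, and an estimate that shifts with whatever baseline imbalance occurs. The baseline score is already needed for the t-test, so using it better takes no extra data.

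**Working it through.** **Inputs from the documents.** Difference 5, sigma 3, alpha 0.05, power 0.80 (section 12); 30 per arm (Study size); final and interim level 0.0294 (section 12 and SAP); interim at 20 patients (section 12).

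**Assumptions.** (a) Sigma = 3 is the SD of change; the protocol does not say, but pairs it with a difference in score change. (b) Equal variances at baseline and two weeks. (c) Rho from 0.3 to 0.9. (d) A 2.2-point effect, purely as an illustration. (e) An equal split, 10 per arm, at the interim.

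**The plan's own figure.** 2 × (1.96 + 0.842)² × 3² / 5² = 5.65, rounded up to 6. It reproduces. At 0.0294 the same formula gives 7.

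**Variance ratio.** With single-score variance s², Var(change) = 2s²(1 − rho) and the residual variance after adjustment is s²(1 − rho²). The ratio is (1 + rho)/2.

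**Precision at 30 per arm.** The change-score standard error is 3 × √(2/30) = 0.775. The adjusted one is 0.775 × √((1 + rho)/2).

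| rho | variance ratio | adjusted SE | SE reduction | same precision as 60 patients needs |
|---|---|---|---|---|
| 0.3 | 0.65 | 0.624 | 19% | 39 |
| 0.5 | 0.75 | 0.671 | 13% | 45 |
| 0.7 | 0.85 | 0.714 | 8% | 51 |
| 0.9 | 0.95 | 0.755 | 3% | 57 |

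**Power (noncentral t, two-sided 0.0294).** The adjusted analysis uses SD 3 × √((1 + rho)/2) and one degree of freedom fewer.

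| case | t-test on change | rho 0.3 | 0.5 | 0.7 | 0.9 |
|---|---|---|---|---|---|
| 5 points, 30 per arm | 0.99998 | >0.9999 | >0.9999 | >0.9999 | >0.9999 |
| 2.2 points, 30 per arm | 0.73 | 0.90 | 0.85 | 0.80 | 0.75 |
| 5 points, 10 per arm | 0.90 | 0.98 | 0.97 | 0.94 | 0.91 |
| difference detectable with 80% power, 30 per arm | 2.39 | 1.93 | 2.07 | 2.20 | 2.33 |

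**Cost of estimating the slope.** The ratio above omits it. A small-sample factor of 1 + 1/(N − 4) allows for it.
- N = 60: the factor is 57/56, and the gain vanishes only at rho of about 0.97. Simulated variance ratios were 0.67, 0.76, 0.87 and 0.97, and both estimators were unbiased.
- N = 20: the factor is 17/16, and the gain vanishes at rho of about 0.88. Simulated interim power for 5 points was 0.98, 0.95, 0.93 and 0.90, against 0.90 for the t-test. At rho 0.9 there is no gain at the interim.

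**Chance imbalance.** The change-score estimate shifts by (1 − rho) times the baseline difference between arms. For an imbalance of one standard error, that is 0.775 × √((1 − rho)/2) = 0.46, 0.39, 0.30 or 0.17 points at rho 0.3, 0.5, 0.7 and 0.9.

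**How plausible is each rho?** An SD of change of 3 implies a single-score SD of 3/√(2(1 − rho)): 2.5, 3.0, 3.9 and 6.7. The largest SD possible on a 0-15 scale is 7.5. Under assumption (a), rho near 0.9 is therefore unlikely, and the smallest gains in the tables are the least plausible.

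**If sigma = 3 is instead the SD of a single score,** the variance ratio is unchanged. For a 2-point effect, power goes from 0.48 to 0.68 (rho 0.3), 0.64 to 0.77 (rho 0.5) and 0.86 to 0.91 (rho 0.7).

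**The case against.** The strongest reply is that nothing needs mending. The hypothesis concerns mean change and the t-test addresses it directly. At the protocol's own smallest relevant difference, power with 30 per arm is about 1, and still 0.998 with 20 per arm. It is 0.95 even for 3 points. The 2.2-point illustration is under half the planned difference and is not from the documents; nor is rho. The test has been in the protocol since 2014, and the SAP is dated June 2019, so replacing it would be a late change to the primary analysis.

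Most of this stands as a limit on the point's weight. It does not remove the gain. The 5 points and the SD of 3 rest on clinical experience with a newly devised composite and a drug untested in this condition, so a smaller effect is possible. Complete-case exclusion also shrinks the sample: at 25 per arm and 2.2 points, power is 0.64 against 0.83, 0.77, 0.71 and 0.66 across the four values of rho. A narrower interval is useful in an exploratory phase 2 trial whatever the p-value.

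A reader might infer more than the documents support:
- **That the plan ignores baseline.** It does not; it subtracts it.
- **That the t-test is biased or invalid.** Over randomisations it is unbiased and holds its level. The shift with imbalance is conditional on the trial as realised.
- **That the primary endpoint is underpowered.** At the planned effect it is not.
- **That a floor effect is established.** No baseline distribution is given, and a linear adjustment would not fully cure one.

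**Conclusion.** The point holds as one of efficiency. The planned test is valid but generally less precise than an analysis that estimates the baseline slope, and neither document provides such an analysis. The variance reduction is 35% to 5% for rho from 0.3 to 0.9, given equal variances; rho is an assumption throughout. The power figures also rest on reading sigma as the SD of change. At the planned 5 points with 30 per arm the choice makes no practical difference to power. It matters for the confidence interval, for true effects well below 5 points, after exclusions for missing scores, and at the interim unless rho is about 0.88 or more. It is a worthwhile improvement to make before unblinding, not a condition for a valid trial.

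**What to change.** By a documented amendment before unblinding, make the primary analysis a linear model of the two-week composite score (or the change; the treatment coefficient is the same) on treatment, with the baseline composite as covariate. Test the treatment coefficient two-sided at 0.0294, with the same model at both looks. Report the t-test on change as a sensitivity analysis.

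Because the t-test is written into protocol sections 6 and 12 as well as the SAP, the amendment must cover both documents and record that it was made blind to allocation. If the interim has already been analysed with the t-test, the amendment should say so; the less disruptive course is then to keep the t-test as primary and pre-specify the adjusted model as supportive.

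The cost is one degree of freedom and the amendment. No further data are needed.

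### The secondary linear models assume one variance and one correlation across 0, 2 and 10 weeks with no safeguard, so their standard errors may be wrong in a direction the documents cannot determine; the free baseline term also costs precision

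*Supplement*

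**What the plan says.** All of this is in the Statistical Analysis Plan, in the paragraphs on secondary analyses. The outcomes are the composite score, its five sub-scores, the composite in a high-risk subgroup, the EQ-5D-3L index and the EQ-5D visual analogue scale.

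- Data: "we will include the observations collected at all time-points, baseline, two weeks, and ten weeks".
- Main effects, besides a constant: "an indicator variable for the treatment group, and an indicator variable for the two-week time-point, an indicator variable for the ten-week time-point".
- Interactions, which give each follow-up visit its own treatment term: "the two interaction (product) terms between the treatment indicator and the time-point indicators".
- Covariates: "Because patients were randomized to either treatment group, we will include no other covariates".
- Within-patient dependence: "The models will also include a patient-specific random intercept, which we will assume to follow a normal distribution independent of all the covariates".
- Test: "We will test the difference between the two treatment groups with the Wald's test using the parameter estimates from the random effects regression models".

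The SAP names no other covariance structure, robust variance or sensitivity model. The primary endpoint is handled apart from these models, as a comparison of mean change to 2 weeks: "We will test this hypothesis with a two-sided t-test at the 0.0294-level".

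**The concern.** In a linear model, a random intercept with independent residuals gives every visit the same variance and every pair of visits the same correlation. The visit pairs here are 2, 8 and 10 weeks apart, and a single dose is given after the baseline assessments. Nothing in the documents supports equal correlations or variances in that setting. If they are unequal, the point estimates still hold with complete data, because the mean model is saturated. One pooled within-patient variance would then serve contrasts whose true variances differ, and the confidence intervals and p-values would be off.

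The second part is efficiency. With this coding the treatment coefficient is the difference between arms at baseline, before any dose. Randomisation makes its expected value zero, yet the model estimates it freely. The SAP uses randomisation to justify leaving out covariates; the same argument justifies a common baseline mean.

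All 10-week efficacy inference, the sub-scores, the high-risk subgroup and both EQ-5D outcomes rest on these models.

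**Working it through.** **The plan's own figure.** The only design calculation is for the primary endpoint (protocol section 12, Primary endpoint): 2 × (1.96 + 0.842)² × 3² / 5² = 5.65, rounded up to 6. It reproduces but has no bearing on the secondary models, for which the documents give no correlation, SE or power.

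**Inputs.** Thirty patients per arm (protocol section 12, Study size). The SAP states no level for the secondary tests, so I use a nominal two-sided 5%, the protocol's "5% risk of rejecting a correct null hypothesis". The correlations below are assumptions. Unless noted, SDs are equal across visits and data are complete. The calculation does not cover logit-linked models.

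**Step 1: SE from the specified model.** Let n be the number per arm and s²e the residual variance. With balanced data the REML fit gives both treatment-by-visit terms

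SE(model) = √(4 s²e / n), where 2 s²e = the mean of Var(Y2 − Y0), Var(Y10 − Y0) and Var(Y10 − Y2).

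A fitted mixed model on simulated data agreed with this formula: 0.1987 for both terms.

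**Step 2: true SE.** At week k, SE(true) = √(2 Var(Yk − Y0) / n). The ratio is therefore √(2 s²e / Var(Yk − Y0)), which with equal SDs becomes √((1 − mean ρ) / (1 − ρ0k)).

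Example with correlations 0.80 (0–2 weeks), 0.50 (0–10) and 0.60 (2–10): mean ρ = 1.90 / 3 = 0.633. Week 2: √(0.367 / 0.20) = 1.35. Week 10: √(0.367 / 0.50) = 0.86.

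**Step 3: range.** Levels come from 20,000 null simulations per row.

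| Assumed ρ: 0–2 / 0–10 / 2–10 wk | Wk 2 SE ratio | Wk 2 level | Wk 10 SE ratio | Wk 10 level |
|---|---|---|---|---|
| 0.60 / 0.60 / 0.60 | 1.00 | 0.050 | 1.00 | 0.054 |
| 0.70 / 0.55 / 0.60 | 1.13 | 0.028 | 0.92 | 0.075 |
| 0.80 / 0.50 / 0.60 | 1.35 | 0.009 | 0.86 | 0.098 |
| 0.50 / 0.50 / 0.80 | 0.89 | 0.084 | 0.89 | 0.082 |
| 0.40 / 0.60 / 0.50 | 0.91 | 0.076 | 1.12 | 0.031 |

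Unequal variances change the picture again. With ρ = 0.60 throughout and SDs in the ratio 1 / 1.3 / 1.3, both SEs are about 3% too large. The range depends on the cases chosen: a correlation falling as 0.97 per week would give 1.74 and 0.83.

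**Step 4: free versus common baseline.** For one follow-up visit and equal SDs, the change contrast has variance proportional to 2(1 − ρ), and the common-baseline contrast to 1 − ρ². Their quotient is (1 − ρ²) / (2(1 − ρ)) = (1 + ρ) / 2.

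- ρ = 0.5: 0.75, a 25% lower variance.
- ρ = 0.7: 0.85, a 15% lower variance.

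On the SE scale, the change contrast is 1.24, 1.15 and 1.05 times the common-baseline contrast at ρ = 0.3, 0.5 and 0.8.

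**The case against.** A reader might infer three stronger claims. The documents do not support them.

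- *The SEs will be wrong in opposite directions: too large at 2 weeks, too small at 10.* That needs correlation that decays with the gap between visits and roughly equal variances, and the documents report neither. The fourth row of the table is just as plausible. In the cited phase III comparison with leuprolide (protocol section 4, Study drug), suppression was present at 3 days and the recovery medians were 112 and 168 days, although under monthly dosing. The two post-dose visits may therefore be the most alike, and both SEs would then be too small. In the high-risk subgroup, if it is chosen on baseline score, the baseline variance is cut. With assumed SDs 0.5 / 1 / 1 and correlations 0.35 / 0.30 / 0.60, the ratios are 0.99 and 0.96, almost no distortion.
- *The free treatment term biases the effect.* It does not. The interactions are valid differences in change from baseline and match the primary estimand. Only precision is lost.
- *The Wald test will be run on the baseline difference.* The SAP does not say so. It includes both interactions and defines the primary effect as a change, so the interactions are the natural reading. The gap is only that the contrast is not named.

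Two further defences carry weight. Small-sample degrees of freedom matter little: in the correctly specified row the large-sample test ran at 0.050 and 0.054. The consequence is also limited, because the protocol calls the trial exploratory, the secondary tests carry no stated level, and the primary test is separate.

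None of this defends equal correlation and variance as an assumption. It is a special case, adopted with no alternative, and a better method costs little.

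**Conclusion.** The point holds in a limited form. The secondary linear models assume compound symmetry across unequally spaced visits and name no unstructured or robust alternative. The 2-week and 10-week SEs may therefore be wrong, and the documents cannot say in which direction. Across the five assumed patterns, model SE over true SE runs from about 0.86 to 1.35 and the actual level from about 1% to 10%; with equal correlations and variances the error is nil. Separately, the free baseline term gives up precision that randomisation makes available, by the factor (1 + ρ) / 2 in variance. These figures rest on assumed correlations, complete data and 30 per arm. The primary analysis is untouched.

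**What to change.** For the numeric secondary outcomes:

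1. Replace the random intercept with an unstructured 3x3 within-patient covariance. Where that cannot be fitted, which is most likely in the high-risk subgroup, use cluster-robust SEs.
2. Drop the treatment main effect so that both arms share one baseline mean. Keep the two visit indicators and the two products.
3. State that the tests are of the treatment-by-2-week and treatment-by-10-week terms.

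Small-sample degrees of freedom are optional. The cost is a few sentences of SAP text, a changed model statement and four more covariance parameters (six instead of two), which 60 planned patients with three visits should support. No new data are needed.

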### Methodology

**Study design:** Phase 2. Investigator initiated. Double-blind, randomized, placebo-controlled. Two parallel groups.

**Dose:** At the same time 2 subcutaneous injections degarelix à 120 mg. Evaluation 2 weeks after injection, and after 10 weeks.

**Primary hypothesis:** Degarelix effective as acute treatment preparations for lowering the risk of child sexual abuse in pedophilia?

**Parameter of efficacy:** A composite measure of self-rated risk and the four most significant risk factors: abnormal sexual orientation (occurrence of pedophilia), preoccupation of sexual thoughts, lack of self-control and low empathy. Each risk factor is evaluated in terms of (i) self-reported intensity, (ii) neuropsychological testing, as well as potential (iii) presumed biomarker--lab--- and Magnetic resonance imaging--- (MRI---) based investigations.

**Safety parameters:** 12---lead---EKG, Osteoporosis Self-Assessment Tool for Men (OST), lab (on all visits: **fb--glucose, hbA1c and fS--insulin, as well as Na, K, Creatinine, ASAT, ALAT, gamma-GT, ALP**) and MADRS-S (self-estimation of depressiveness, includes a question of suicidality). Annual safety and SUSAR reporting, in collaboration with KTA.

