### Secondary endpoints

1. Adverse events, SUSAR, side effects.

2. Effect on supposed biomarkers for risk factors. Hypothesis: The effect of the different treatment arms on the biomarkers of risk factors differs statistically significantly among themselves.

Risk factor 1. Presence of pedophilia. Measuring instruments: functional MRI/Not Real People Paradigm (27).

Risk factor 2. Busyness with sexual thoughts. Measuring instruments: functional MRI/resting state.

Risk factor 3. Lack of self-regulating ability. Measuring instrument: counting Stroop (28).

Risk factor 4. Low empathy. Measuring instruments: functional MRI/affective faces paradigm.

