### Assessment of clinical safety

Patients are excluded if on the first day of visits turn out to have:

- ☐ 12-lead-EKG with QT/QTc-interval > 450 ms.
- ☐ Outside reference range on the following samples: Na, K, Creatinine, ASAT, ALAT, gamma-GT, ALP indicating kidney failure or impaired liver function.
- ☐ Osteoporosis Self-Assessment Tool for Men (OST) indicating severe osteoporosis
- ☐ MADRS-S indicating deep depression, or presence of severe suicidal thoughts

Patients are monitored with respect to glucose intolerance and possible diabetes, with the following samples each visit:

- ☐ fB-glucose, hbA1c och fS-insulin

On the first visit, as well as at 2-week- and 10-week follow-up, fB-glucose, hbA1c and fS-insulin, as well as to Na, K, Creatinine, ASAT, ALAT, gamma-GT, ALP.

All samples are labelled for immediate analysis, and the test results are assessed by doctors on the day of the visit so that medical measures can be taken on the same day.

AE/SAE-reporting takes place in cooperation with KTA.

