### Analysis response assessment -- efficiency and safety parameters

Efficacy responses are only compiled after the end of the study. However, all patients will be asked to enroll at CASM after participation. Then the current situation and treatment needs can be discussed again. Patients who feel they need urgent medical or psychiatric help during the course of the study are urged to call PrevenTell, or seek psychiatric or medical emergency rooms.

Assessment of clinical safety is carried out continuously. The doctor assesses on the visiting day ECG, OST, lab samples as above and MADRS-S. Unwanted medical events are handled as below. Patients also receive a booklet, a side effects diary, where they can fill in retrospectively what they adverse health effects of treatment they experience, and are encouraged to include it on follow-up.

The annual report, an annual security report to the Swedish Medicines Agency and the Ethics Review Committee, will be done in collaboration with KTA.

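### No by-arm summary of change in fasting glucose, HbA1c or insulin is planned: apart from an unspecified interim safety look, the only stated safety method is a frequency table of binary side effects

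*Supplement*

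**What the plan says.** **What is collected.** The protocol summary (section 1, Methodology) lists the safety parameters: ECG, the osteoporosis tool, a laboratory panel at all visits that includes fB-glucose, HbA1c and fS-insulin, and "MADRS-S (self-estimation of depressiveness, includes a question of suicidality"). Section 10 (Assessment of clinical safety) gives the purpose of the glucose set: "Patients are monitored with respect to glucose intolerance and possible diabetes, with the following samples each visit". It repeats the laboratory panel at the first visit, 2 weeks and 10 weeks. Section 6 (Sampling in the study) says the samples serve both to monitor the men and to answer the primary and secondary endpoints.

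**What safety question is asked.** Secondary hypothesis 1 asks which side effects go with degarelix in this patient group. The matching secondary endpoint is "1. Adverse events, SUSAR, side effects".

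**What analysis is planned.** The SAP opens with "The statistical analysis will proceed as stated in the study protocol". After the primary test it says "we will perform secondary analyses to evaluate differences between the treatment groups with respect to each of the following outcomes separately", and lists the composite score, its five sub-scores, the composite in a high-risk subgroup, the EQ-5D-3L index and the EQ-5D visual analogue scale. Safety then gets one sentence: "The number of possible side effects (binary variables) will be summarized by frequency tables by treatment group". Section 12 of the protocol adds a preliminary analysis of efficacy and safety after 20 individuals, without naming safety variables or a method.

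**What happens to individual values.** Section 10 says "The doctor assesses on the visiting day ECG, OST, lab samples as above and MADRS-S". Section 11 allows abnormal laboratory results to be assessed as clinical events, and all adverse events are entered in the CRF.

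**The concern.** Three numeric variables are measured at three time points, for a named metabolic risk, in a randomized placebo-controlled trial, and no summary by arm is assigned to them. The stated safety method works on yes/no variables. A moderate rise in fasting glucose or insulin across the degarelix arm, with few men crossing the level at which an event is recorded, would leave little or no trace in such a table.

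At stake is secondary hypothesis 1. The protocol says degarelix has not been tested in pedophilia, and its main cited safety source is an open-label study against leuprolide in prostate cancer patients of median age 72. This trial treats men aged 18 to 65 and compares them with placebo, so the change in these values by arm is information that the background studies do not supply. Section 12 also gives safety as one reason to go on to full size after the interim.

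**Working it through.** **1. The plan's own figure.** No figure in the documents concerns the safety analysis. The one calculated sample size is for the primary endpoint (section 12): N = 2 × (1.96 + 0.842)² × 3² / 5² = 5.65, which rounds up to the stated 6 per arm. It reproduces. It bears on this point only in that the 30 per arm come from the secondary objectives, as Study size says.

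**2. Collection set against analysis.**

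| Variable | Named as safety parameter | Post-injection visits stated | By-arm summary of change planned |
|---|---|---|---|
| fB-glucose, HbA1c, fS-insulin | Yes (sections 1, 10) | 2 and 10 weeks | None |
| Sodium, potassium, creatinine, ASAT, ALAT, gamma-GT, ALP | Yes (sections 1, 10) | 2 and 10 weeks | None |
| MADRS-S | Yes (section 1) | Not clear (step 4) | None |
| Side effects | Yes (section 6) | Adverse event reporting at visit 2; diary for follow-up | Frequency table |

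The SAP has a suitable tool: "The regression models will be linear for the numeric outcomes and logit-linked for the binary ones". It attaches that model to the listed outcomes only, and no laboratory value or MADRS-S score is among them. Deferring to the protocol does not fill the gap, since section 12 gives no method for these values either.

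**3. Other routes into the results.**
- *Interim look at 20 men.* Content is not stated, so it neither guarantees nor excludes these values. If it did include them, with about 10 per arm (assumed even split), the half-width of a 95% CI would be t(0.975; 18) × √(2/10) = 2.101 × 0.447 = 0.94 SD.
- *Adverse event recording.* An abnormal value may become an event and enter the table. No rule says when, and a shift that stays below that level does not.
- *Same-day physician review.* This works patient by patient and cannot show a difference between arms.
- *Annual safety report.* No by-arm summary of laboratory values is described.

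**4. MADRS-S schedule.** In section 1 the phrase about all visits sits inside the laboratory bracket. Section 10 uses MADRS-S as a first-day exclusion check and leaves it out of the list repeated at 2 and 10 weeks. The following subsection has it assessed on the visiting day without saying which. The documents shown do not settle when it is given after injection.

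**5. What the collected data could deliver.** Inputs: 30 per arm (Study size), two-sided 95% confidence, approximate normality (assumed). The documents give no SD for these variables, so results are in SD units.
- Unadjusted half-width: t(0.975; 58) × √(2/30) = 2.00 × 0.258 = 0.52 SD.
- With 25 evaluable per arm: 0.57 SD.
- With baseline adjustment at an assumed correlation of 0.5, the residual variance factor is 1 − 0.5² = 0.75, so the half-width is about 0.52 × √0.75 = 0.45 SD.
- Difference detectable with 80% power at two-sided 0.05, unadjusted: 0.74 SD at 30 per arm, 0.81 SD at 25.

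**6. Illustration of what the table shows.** Assume a 0.75 SD shift and an event level that 5% of placebo men cross. The degarelix rate is then 1 − Φ(1.645 − 0.75) = 0.185, so the expected counts are 30 × 0.05 = 1.5 and 30 × 0.185 = 5.6. The shift and the rate are assumptions. They show how a group shift thins out in a yes/no table, and nothing in the conclusion depends on them.

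**The case against.** The strongest reply is that the plan matches its own endpoint. Safety is defined by events, the hypothesis asks about side effects, and the SAP tabulates side effects by arm. The glucose samples are described as patient monitoring, read the same day so that a doctor can act. In a phase 2 exploratory trial, modelling monitoring values might be called preference. This stands in part: the primary result is untouched and no formal test is needed. But the sampling section says the blood is also drawn to answer the endpoints, so individual care is not its only purpose.

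A reader might infer that the frequency table is the only safety analysis, that the metabolic values would never be compared, and that a drift would go unreported. The documents do not support this. An interim safety analysis is planned, though undefined. The plan is silent on numeric laboratory values and does not bar their reporting. Abnormal results can be recorded as events. The list of binary side effects is not given, so out-of-range flags may be among them.

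A reader might also rest the case on power. Under assumed placebo event rates of 2.5% to 10%, Fisher's exact test has 6% to 36% power for a 0.75 SD shift, against about 82% for a comparison of means. That is an illustration only: the plan states no test of the table, and the remedy is descriptive too. At 0.5 SD the unadjusted comparison of means reaches only 48%.

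Finally, men outside the reference range for liver, kidney and electrolyte values are excluded at entry. Baseline-to-worst shift tables would then reduce largely to counts of new abnormalities. That objection stands, and simple counts suffice for those values.

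**Conclusion.** The point holds in a limited form and the plan should be changed. No by-arm summary of change is prespecified for fB-glucose, HbA1c or fS-insulin, although all three are named safety parameters drawn at three visits for a stated risk. A group shift below the adverse-event level has no planned place in the results. This rests on reading the documents side by side and needs no assumed effect size.

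The size is moderate. The primary analysis is unaffected; what weakens is the answer to secondary hypothesis 1. The unused information amounts to a between-arm estimate with a half-width of about 0.5 SD per variable and visit, assuming 30 evaluable men per arm and roughly normal values. That is enough to reveal a large shift or make one unlikely, and not enough to exclude a small one.

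For MADRS-S the point is conditional: it applies only at the follow-up visits where the scale is given.

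**What to change.** Add a short safety paragraph to the SAP:

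- For every injected man with data, report the by-arm mean difference in fB-glucose, HbA1c and fS-insulin at 2 and 10 weeks, each adjusted for its own baseline, with a 95% CI. State the scale of analysis (raw or log) in advance.
- Do the same for the MADRS-S total at whichever follow-up visits it is given. The Methodology summary and the two safety-assessment subsections of section 10 must be reconciled on that schedule.
- Count new out-of-range liver, kidney and electrolyte values by arm.
- Keep the side-effect frequency table.
- Label all of these as descriptive safety estimates outside the 0.0294 test.

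The laboratory part uses data already collected and needs no new visit or procedure, only a few more tables. The drawback is several intervals without multiplicity adjustment, some of which may look notable by chance; the label should say so.
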